#### The therapeutic NMES arm

Patients will be blinded as to which arm of the trial they are in. Therapeutic NMES will be delivered by a *MicroStim Exercise Stimulator* MS2v2 using two self-adhesive electrodes placed on the anterior thigh over the body of the vastus medialis and vastus lateralis muscles and the lower back.

Pulse waveform (symmetrical biphasic squared), frequency (40 Hz), and width (350 microseconds) would be used for the duration of treatment with the NMES. The amplitude (device output 0–120 mA, tested across 1000Ω) will be set to elicit a visible and comfortable muscle contraction; patients will be encouraged to subsequently increase the amplitude as tolerated. A “compliance diary” will be kept by the patients during their treatment period detailing their time spent using the device and the settings at which they are using it.

This programme is adapted from one found to be of benefit in a pilot study of patients with non-small cell lung cancer which itself was based on an NMES exercise programme developed for patients with COPD. The stimulation parameters were selected to favour gains in function and strength over endurance (frequency), minimise skin irritation (pulse width) and allow for sufficient recovery of the muscles between contractions (duty cycle) [13, 19].

#### The placebo NMES arm

A modified model of *MicroStim Stimulator* MS2v2 (*Odstock Medical Limited, Wiltshire, UK*) will be provided to the placebo group who will apply two self-adhesive electrodes placed on the anterior thigh over the body of the vastus medialis and vastus lateralis muscles and the lower back as in the treatment group. This placebo device will be programmed to provide sub-therapeutic electrical stimulation. The device manufacturers have tailored a programme to come on and off at specified timings with ramps of specified duration. The placebo devices output is restricted to around 18V and this gives little or no muscle recruitment. Patients will however perceive a sensation of electrical stimulation.

#### Both groups

Patients in both arms will receive standard care including enhanced nutritional support (parenteral nutrition for a minimum of 5 days or until taking sufficient calories enterally) and physiotherapy in line with current guidelines and local hospital practices. Routine daily blood tests for inflammatory markers will be taken until discharge.

### Assessment of outcomes

Patients from both the treatment and control arms will receive standard 5-year follow-up. Histopathological data will be recorded following processing of the resected specimens by the pathologist. Quality of life data, patient satisfaction, bio-impedance analysis, CT Body composition and functional measurements will be taken as detailed below.

As a phase II trial, we aim to determine the short-term effects on our primary outcome; as such, our primary analysis to identify changes within the pre- and post-operative CT scans and analysis of NMES satisfaction and the initial inflammatory data, functional and quality of life data will take place at 6 months following the recruitment of the final patient with subsequent reporting and publication of these results. We will then continue long-term follow-up for the standard clinical 5-year follow-up period or until patient death. Final analysis exploring the effect of intervention on 5-year overall and disease-free survival will take place at 5 years following recruitment of the final patient.

### Body composition assessment

#### CT body composition parameters

CT image analysis using *SliceOmatic* version 5.0 software (*TomoVision, Montreal, Quebec, Canada*) will be performed. Total skeletal muscle and visceral adipose tissue surface area (cm^2^) will be evaluated on a single image at the third lumbar vertebra (L3) using HU thresholds of −29 to 150 for skeletal muscle, −50 to 150 for visceral adipose tissue (VAT) and −190 to −30 for subcutaneous adipose tissues. CT body composition analysis of all the included images will undergo automated segmentation using the ABACS L3 automated plug-in software [26] (*Voronoi Health Analytics, BC, Canada*), which complements SliceOmatic. The automated process will be directed by a radiologist who will be blinded to the treatment group of individual patients. The automated segmentation process provided by the ABACS L3 plug-in also removes the possibility of operator bias in the analysis of the images. The sum of skeletal cross-sectional muscle areas will be normalised for stature (m^2^) and reported as lumbar skeletal muscle index (LSMI) (cm^2^/m^2^). Outcome variables will be continuous; categorical variables will be defined from these data using the cut-off values described earlier [20, 27, 28].

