#### Secondary outcomes

Our main secondary outcomes include change in total skeletal muscle cross-sectional area, at the L3 level between treatment and non-treatment groups as well as between time points for individual patients. Difference in quality of life between groups using the validated questionnaires ED-5Q-5L & EORTC QLQ – CR29. Post-operative complications and length of hospital stay between both arms and comparison of the systemic inflammatory response between each group. A comprehensive list of secondary outcomes is shown in Table 2.

**Table 2 Tab2:** Secondary outcomes

Domain	Specific measurement	Metric	Method of aggregation	Time point
Lumbar skeletal muscle index (LSMI)	The difference in lumbar skeletal muscle index (LSMI=height / area of skeletal muscle in cm^2^ at L3) derived from the third lumbar vertebral axial level	Change in LSMI at each time point	CT Scan; SliceOmatic software version 5.0 with ABACS L3 Plug-in automation tool	Pre-surgery 3 to 6 months post-surgery
Visceral adipose tissue (VAT) Surface area	Visceral adipose tissue area (cm^2^) derived from the third lumbar vertebral axial level	Change in VAT at each time point	CT Scan; SliceOmatic software version 5.0 with ABACS L3 Plug-in automation tool	Pre-surgery 3 to 6 months post-surgery
Systemic inflammation	C-Reactive Protein and serum albumin	Modified Glasgow Prognostic Score	Ordinal values mGPS=0 mGPS=1 mGPS=2	Preoperatively and 6 months post-surgery
Cellular immune response	Neutrophil count Lymphocyte count	Neutrophil to lymphocyte ratio (neutrophil/lymphocyte count	Clinically relevant categorical cut off values NLR<3 NLR>3	Pre-operatively and 6 months post-surgery
Post-operative complications	Any post-operative complication	Clavien-Dindo Classification	Clavien-Dindo Score 1–5	Between 0 and 90 days post-surgery
Length of hospital stay	Inpatient stay post-surgery	Days	Median length of stay	From surgery to hospital discharge
Disease-free survival	Days to reported first recurrence / death / 5 years post-surgery	Days	Kaplan-Meier survival analysis	From date of surgery to 5 years post-surgery
Overall survival	Days to death / 5 years post-surgery	Days	Kaplan-Meier survival analysis	From date of surgery to 5 years post-surgery
Quality of life (General)	EuroQol 5-level EQ-5D5L Mobility, self-care, usual activities,	Visual analogue scale score 1–100 and score in each of the 5 domains	Change in scores between events	Pre-surgery, 6 and 12 months post-surgery

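### Two CT secondary outcomes are misdefined in print: the visceral-fat HU window contains the whole muscle window, and Table 2 inverts the LSMI given in the methods text

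*Protocol article*

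**What the plan says.** The Protocol article, section CT body composition parameters, gives three density windows for the L3 image:

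- Muscle: "HU thresholds of −29 to 150 for skeletal muscle".
- Visceral fat, where the same sentence runs on, shown from just after its first minus sign: "29 to 150 for skeletal muscle, −50 to 150 for visceral adipose tissue (VAT").
- Subcutaneous fat, after a minus sign: "190 to −30 for subcutaneous adipose tissues".

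No other VAT window appears in the article. VAT area at L3 is a secondary outcome in Table 2.

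LSMI is defined twice. Table 2, under Secondary outcomes, has "LSMI=height / area of skeletal muscle in cm^2^ at L3". The CT section says that muscle area is "normalised for stature (m^2^) and reported as lumbar skeletal muscle index (LSMI) (cm^2^/m^2". The same section adds that categorical variables will be formed from the continuous measures using published cut-offs.

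Both outcomes are to be obtained with SliceOmatic 5.0 and the automated ABACS L3 plug-in, under a blinded radiologist.

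**The concern.** A fat window that runs up to the top of the muscle window does not define fat. On the article's own figures, subcutaneous fat ends at −30 and muscle starts at −29, so the two do not overlap. The printed VAT window ignores that boundary. If it were applied, VAT area would leave out most of the fat-density range and admit tissue that is not fat.

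For LSMI, the two definitions point in opposite directions. An analyst working from Table 2 would compute an index that rises as muscle is lost, and a benefit would read as a harm. Changing the sign afterwards would not repair it, because the Table 2 quantity is proportional to the reciprocal of area. The baseline-adjusted ANCOVA planned for continuous secondary outcomes would then estimate something different. The Table 2 index is also on another scale from cm²/m², so cut-offs on that scale could not be applied to it.

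**Working it through.** **Plan's own figure.** The only calculated figure in the article is the sample size, and it uses neither definition. With SD 9.4 HU, correlation 0.3, difference 8 HU, 5% significance (taken as two-sided) and 90% power, the adjusted SD is 9.4 × √(1 − 0.3²) = 8.97. This gives 27 per group and 54 in total, as stated. 54 / 0.95 rounds up to 57, and the stated 58 is the next even number. Nothing below changes this.

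**1. VAT window.** Inputs are the three printed windows, counted in integer HU values (upper − lower + 1).

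| Window | Range | Values |
|---|---|---|
| Muscle | −29 to 150 | 180 |
| VAT as printed | −50 to 150 | 201 |
| Subcutaneous fat | −190 to −30 | 161 |

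- Muscle and VAT: overlap −29 to 150 = 180 values. That is 180/180 = 100% of the muscle window and 180/201 = 90% of the VAT window.
- Subcutaneous fat and VAT: overlap −50 to −30 = 21 values, or 21/161 = 13% of the fat window. The remaining 140 values (−190 to −51) are excluded.
- Subcutaneous fat and muscle: overlap 0.

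These percentages are shares of a density scale. They are not shares of pixels or of area.

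One candidate for the intended window is −150 to −50, which assumes a lost minus sign and swapped bounds. It would overlap muscle by 0 values and lie wholly inside the subcutaneous-fat window (101 of 101 values). The document does not state it.

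**2. LSMI.** Height and areas are assumed for illustration: 1.70 m, with L3 muscle area falling from 140 to 120 cm² (−14%).

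| Definition | At 140 cm² | At 120 cm² | Change |
|---|---|---|---|
| CT section: area / height² | 140 / 2.89 = 48.4 cm²/m² | 120 / 2.89 = 41.5 cm²/m² | −14% |
| Table 2: height / area | 1.70 / 140 = 0.0121 | 1.70 / 120 = 0.0142 | +17% |

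For one patient height cancels, so the Table 2 index changes by 1/(1 − loss) − 1. An area loss of 5%, 10% or 20% gives a rise of 5.3%, 11.1% or 25%. The direction does not depend on the assumed height. Table 2 also leaves height unsquared, so its units cannot match cm²/m².

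**The case against.** The strongest reply is that these are misprints with limited reach.

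- *LSMI is already right in the CT section.* That text gives the direction, the squared height and the units. This stands. The fault is a contradiction confined to one table cell, and the index rises with muscle loss only if Table 2 is followed.
- *Segmentation is automated.* The article does not say whether the typed thresholds are entered or the software applies its own. This stands too, so the VAT consequence is conditional. Segmentation by anatomical region might also keep skeletal muscle out of the VAT area, although the printed window would still exclude most of the fat-density range.
- *Nothing decisive is touched.* Mean muscle attenuation uses the muscle window, which is not in question. The opening text on secondary outcomes does not single out VAT among the main ones; it appears in Table 2.

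A reader might infer more than the document supports. One such inference is that 90% of measured VAT would be muscle, but the 90% only counts HU values. Another is that the sarcopenia assessment fails with LSMI. The Data collection section attaches the term sarcopenia to muscle area, and change in raw L3 area is itself a main secondary outcome that the formula does not touch. A third is that trial results are already wrong; nothing shows that the printed settings were used.

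What remains is that both definitions are wrong as printed. A text-extraction fault is unlikely for VAT, because the other minus signs in the same sentence survive.

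**Conclusion.** Two secondary outcome definitions need correction, at moderate severity.

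The VAT window cannot be right on the article's own figures: it contains all of the muscle window and only 13% of the subcutaneous-fat window. If it was applied, VAT area would be wrong by an amount that cannot be derived from the document.

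Table 2's LSMI contradicts the CT section in direction, power of height and units. If it was followed, the illustrative 14% fall would be reported as a 17% rise. That size rests on the assumed areas; the reversal does not.

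**What to change.** 1. In the CT section, replace the VAT window with the fat-density range actually set in SliceOmatic/ABACS. Treat −150 to −50 as a guess to be checked against that setting, not as the correction itself.
2. In Table 2, write LSMI = L3 skeletal muscle area (cm²) / height² (m²), in line with the CT section.
3. Before analysis, confirm which VAT thresholds were used for scans already processed. Re-run only those processed with the printed window.

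The cost is two wording corrections and one settings check, plus an automated re-run of VAT only if the printed window was applied.

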#### Anthropometrics and bio-impedance analysis

Bio-impedance analysis (BIA) will be undertaken using a SECA mBCA 525 analyser (*SECA, Hamburg Germany*). This will be performed at baseline, day 2 post-surgery, either hospital discharge or at 28 days post-surgery (whichever is first) and at 6 months. Patients will undergo analysis in a fasted state. Posterior upper arm skin fold thickness and waist circumference will be performed at baseline and 6 months. We will measure thigh circumference at 15cm above the superior pole of the patella (which has been shown in earlier studies to correlate with muscle volume on MRI) [25]. Phase angle from BIA and patient BMI will be utilised as categorical variables with other outcome variables being continuous.

#### Functional assessment

It is important that we measure not only the anatomical effects of NMES, i.e. increased muscle mass on CT and anthropometric changes, but we identify whether these patients demonstrate both a functional and physiological improvement. To that end, we will assess functionality preoperatively at diagnosis and post-operatively at 3 months using the validated instruments of the 6-min walk test [24], 30 s sit-to-stand test [23] and Berg Balance scale (BBS) [21, 22]. These assessments will be undertaken in the complex cancer clinic by either a specialist physiotherapist or research fellow. These data will be treated as continuous outcome variables with the exception of BBS which will be categorical.

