	Pain/discomfort and anxiety/depression			
Quality of life (colorectal specific)	EORTC QLQ - CR29 Function and Symptoms	4 multi-item scales and 19 single items assessing common symptoms and problems in colorectal cancer	Change in score between events	Pre-surgery, 6 and 12 months post-surgery
Function	Berg Balance Scale (BBS)	Berg balance score (0–56)	Change in BBS score	Pre-surgery and 6 months post-surgery
	30 s sit to stand	Number of full sit-to stand actions completed in 30 s	Change in number of successful actions	
	6-min walk test	Distance walked in 6 minutes	Change in metres	
Thigh circumference	Thigh circumference, 5cm above the superior pole of the patella	Circumference in cm	Change in thigh circumference between groups	
Dose response to NMES	Pre- and post-operative mean muscle attenuation (L3) (MMA) and hours of device usage	Change in MMA/time	Linear regression	3–6 months post-surgery
Patient satisfaction	Free text responses and satisfaction scores derived from each domain (see patient satisfaction survey supplementary material).	Qualitative and visual analogue scale 1-10	Qualitative responses Median score between groups on each domain assessed	8 weeks post-surgery
Bioimpedance analysis	Phase angle = (Xc/R)*180°/π	Cellular resistance (R) and cellular reactance (Xc)	Change in phase angle at each time point	Baseline, day 2 post operatively, day 28 postoperatively (if in hospital), day of discharge, first post-operative follow-up appointment

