### Planned statistical analyses

This study will be performed in line with the CONSORT criteria (http://www.consort-statement.org/consort-2010). Initially outliers, patterns of attrition and missing data will be identified using a combination of graphical displays and descriptive statistics allowing decisions on the assumption of normality. The primary analysis will be of observed data only, with patients with missing data omitted from the analysis. If the primary outcome has >10% missing data points, a sensitivity analysis will be performed using multiple imputation to estimate the missing values.

Data will be analysed by a statistician blinded to the intervention. Analyses of primary and secondary endpoints will be based on the full analysis set defined according to the intention to treat principle. Safety analysis will be performed for the on all enrolled individuals with disclosure of any significant adverse events. The full analysis set consists of all participants consented and randomised with valid baseline assessments. Participants will be analysed according to the study arm they were assigned at randomisation.

The primary outcome is myosteatosis at 3–6 months post-surgery, derived from the mean muscle attenuation on CT body composition analysis. This will be analysed using analysis of covariance (ANCOVA), with muscle attenuation values at baseline used as a covariate in the analysis.

The secondary outcome measures measured on a continuous scale, and with a baseline measurement will be analysed using equivalent methods as the primary outcome. For continuous outcomes with no baseline measurement, group comparisons will be made using either the unpaired *t*-test or Mann-Whitney test, depending on data distribution. The chi-square test, or Fisher’s exact test, will be used to compare categorical outcomes between the study groups.

Significance will be assumed when *p*<0.05.

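### Berg Balance score and phase angle are change scores in Table 2 but categories in the text, which moves them from baseline-adjusted ANCOVA to an unadjusted chi-square or Fisher test

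*Protocol article*

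**What the plan says.** **Berg Balance Scale (BBS).** Table 2 lists a score from 0 to 56, aggregated as "Change in BBS score". The Functional assessment section says of the walk test, the sit-to-stand test and the BBS: "These data will be treated as continuous outcome variables with the exception of BBS which will be categorical".

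**Phase angle.** Table 2 gives "Change in phase angle at each time point". The section Anthropometrics and bio-impedance analysis says: "Phase angle from BIA and patient BMI will be utilised as categorical variables with other outcome variables being continuous".

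**NLR.** Table 2 itself sets the categories: "Clinically relevant categorical cut off values NLR<3 NLR>3". It lists no change score.

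**mGPS and Clavien-Dindo.** Table 2 labels mGPS (0, 1, 2) as ordinal and scores Clavien-Dindo from 1 to 5.

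**Tests.** Planned statistical analyses sends continuous secondary outcomes that have a baseline to the same method as the primary outcome, which is ANCOVA with baseline as covariate. For categories it says: "The chi-square test, or Fisher’s exact test, will be used to compare categorical outcomes between the study groups".

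No cut-off or number of categories is stated for BBS or phase angle.

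**The concern.** The words continuous and categorical are not just description here, because the article's own rules use them to choose the test. BBS and phase angle both have a baseline measurement. Read from Table 2, they go to ANCOVA. Read from the text sections, they go to an unadjusted comparison of proportions. The two analyses can give different p-values, and either could be reported as the prespecified one. With no cut-offs stated, the categories could also be chosen after the data are seen.

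The categorical route is also the less precise one. It discards differences within categories and drops the baseline covariate. That matters because the trial is meant to guide a phase III study, and the Functional assessment section stresses showing functional as well as anatomical benefit.

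**Working it through.** **1. Routes under the article's own rules**

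| Outcome | Table 2 | Text section | Resulting test |
|---|---|---|---|
| BBS | change in score | categorical | ANCOVA or chi-square/Fisher: conflict |
| Phase angle | change at each time point | categorical | ANCOVA or chi-square/Fisher: conflict |
| NLR | below 3 / above 3 | marker named only | chi-square/Fisher: no conflict, but exactly 3 is unassigned |
| mGPS | ordinal 0, 1, 2 | marker named only | chi-square/Fisher: order ignored |
| Clavien-Dindo | 1–5 | same classification named | chi-square/Fisher: order ignored, no level for no complication |

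**2. The plan's own sample size, for reference**

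Inputs from Sample size estimation: difference 8 HU, SD 9.4 HU, baseline–outcome correlation 0.3, 5% significance, 90% power. Two-sided testing is not stated but reproduces the figure.

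- Adjusted SD = 9.4 × √(1 − 0.3²) = 8.97.
- n per group = 2 × [8.97 × (1.960 + 1.282) / 8]² = 26.4, so 27.
- With 5% dropout: 27 / 0.95 = 28.4, so 29 per group and 58 in total.

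This agrees with the article. The standardised effect is 8 / 9.4 = 0.85 SD. The article gives no effect size or power for BBS, phase angle or NLR.

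**3. Information lost by a two-way split**

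Assumption: a normal outcome, cut so that a fraction p lies below. Information kept = φ(z_p)² / [p(1 − p)].

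- p = 0.5: 0.3989² / 0.25 = 2/π = 0.637, a loss of 36%.
- p = 0.3: 0.3477² / 0.21 = 0.576, a loss of 42%.
- p = 0.2: 0.2800² / 0.16 = 0.490, a loss of 51%.

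Losing the baseline covariate as well multiplies the information kept by (1 − r²). At the median with r = 0.3: 0.637 × 0.91 = 0.579, a loss of 42%. The value 0.3 is the article's assumption for muscle attenuation, not for these outcomes.

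**4. Illustration in power**

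Assumptions: effect 0.85 SD, 29 per arm, normal outcome, cut midway between the arms. The proportions below the cut are then Φ(0.4255) = 0.665 and 0.335. The t-test figure is from the noncentral t distribution; the others are from exact enumeration of all 2×2 tables.

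| | t-test | chi-square (uncorrected) | Fisher |
|---|---|---|---|
| 0.85 SD, 29 per arm | 89% | 72% | 62% |
| 0.85 SD, 27 per arm | 87% | 67% | 56% |
| 0.5 SD, 29 per arm | 46% | 32% | 23% |

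The t-test column has no baseline adjustment, so the gap to ANCOVA is somewhat wider.

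**5. More than two categories**

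With 3, 4 or 5 equal categories and a test that uses their order, the loss would be about 21%, 14% and 10%. The planned chi-square ignores order, so its approximate power at 27 per group and 0.85 SD is 67%, 63% and 60%. Finer categories do not recover the loss under the planned test.

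**The case against.** The strongest reply is one of scope. These are secondary outcomes in a phase II trial powered only on muscle attenuation, and a separate analysis plan may settle the methods. The scope point stands and limits the weight of the finding. The appeal to an analysis plan does not remove the contradiction, because the article makes two explicit statements about the same outcomes and they disagree. It has more force for mGPS and Clavien-Dindo, where the choice of an ordinal method could reasonably be left to such a plan.

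A looser reading of categorical does not help either. Treating the raw 0–56 score as unordered levels in 58 patients would be worse. For CT measures the article keeps the outcomes continuous and derives categories from them, whereas BBS and phase angle are expressly excepted from continuous handling.

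A reader might infer four stronger points that the article does not support:

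- **That NLR is contradictory too.** Table 2 sets its cut and calls it clinically relevant, so only information loss and the unassigned value can be criticised.
- **That a fixed share, such as a third, of the information is lost.** That figure needs a normal outcome split at the median. The article states no cut for BBS or phase angle, does not place an NLR of 3 at the median, and a bounded 0–56 scale need not be normal.
- **That categorising removes most of the chance of detecting an effect.** In the illustration a power of 89% becomes 72% or 62%, so most of it remains.
- **That early inflammation should be compared because "Routine daily blood tests for inflammatory markers will be taken until discharge".** This would be an added endpoint. The Data collection section states recording of inflammatory markers at elective clinic visits and does not show that daily values enter the case report form. The Assessment of outcomes section already includes initial inflammatory data in the first analysis.

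**Conclusion.** The contradiction holds for BBS and phase angle. Following the text sections as written replaces a baseline-adjusted analysis with an unadjusted and less precise one, using categories that are not defined. For NLR there is no contradiction, only an avoidable loss of information and a boundary gap at 3. For mGPS and Clavien-Dindo, the only tests named for categories ignore an order that the scales carry.

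The article does not fix the size of the loss. Under normality, a two-way split costs about 36% of the information at best and about 51% at 20/80. A median split that also drops a covariate with r = 0.3 costs about 42%. The power figures further assume that the primary outcome's 0.85 SD effect carries over and that all 29 per arm are observed. The primary analysis, its power and the 58 patients are untouched. The change is worth making because it is cheap and removes an ambiguity, but it does not threaten the trial's main conclusion.

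**What to change.** - Reconcile the Functional assessment and bio-impedance sections with Table 2: analyse the Berg score and phase angle as continuous, by ANCOVA with the baseline value, as Planned statistical analyses already provides for such outcomes.
- Analyse NLR as continuous on the log scale by ANCOVA with baseline. Keep the cut at 3 as a descriptive table and assign the value 3 to one side.
- Compare mGPS and Clavien-Dindo by an ordinal method (proportional odds or Wilcoxon), adding a level to Clavien-Dindo for patients with no complication.
- If any BBS or phase-angle categories are kept for description, state their cut-offs before unblinding.

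The cost is analysis wording only. All these measurements are already planned, and the sample size does not change.
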